#### Service providers

Those who are selected by their organizations to deliver My Choice–My Way! to youth participants are referred to as service providers. There were no specific inclusion criteria other than that the organization finds this person to be suitable for delivering the support and the service provider has received the authorized training in My Choice–My Way! The service providers included in the study had different roles within their organization. One thing all service providers have in common is that they interact with youth placed in different forms of out-of-home care in their daily work. All social workers charged with delivering My Choice–My Way! undergo a four-and-a-half-day training prior to starting their work with youth.

### Intervention

In the project, we will test and evaluate My Choice—My Way! (Swe. Mitt val-Min väg!) and Usual Services. Currently, there are no widespread, standardized transitions services for youth leaving care in Sweden.

#### My Choice—My Way!

My Choice–My Way! is delivered individually to youth aged 15 years and older by trained social workers. My Choice-My Way! is based on Self-Determination Theory [33], Social Cognitive Theory [34], and the COM-B Model for Behavior Change [18] as well as findings from prior research on the effects of interventions designed to support youth in their transition from out-of-home care to independent living [35–37]. The manual consists of guidance material provided to the program deliverer (i.e., service provider) as well as information and concrete materials (i.e., a workbook) provided to the youth participant [38, 39]. The youth material is optional, and use is based solely on the individual youths’ desire (i.e., autonomous decision-making) to use the material. The manual consists of 19 chapters divided into three blocks. The first block consists of sessions designed to orient the youth toward the future, the second block consists of a range of knowledge, skill and ability topics and exercises, and the third block consists of sessions designed to re-orient the youth toward the future as well as apply new knowledge, skills and abilities gained through participation in My Choice–My Way!. The 19 chapters are divided into core and optional content. Each chapter includes a short review of research motivating the topic area (as relates to youth transition from out-of-home care and youth developmental tasks), and concrete session goals.

Deliverers are tasked to work with youth through a minimum of 16 chapters (unless the deliverer determines that the youth participant already possesses the knowledge, skill, or ability covered in the material) over a period of 4–8 months. The sessions are designed to be delivered in an order that best suits the youth’s individual needs and deliverers are encouraged to plan sessions based on issues that are of most relevance to the youth in attaining their self-identified goals. My Choice–My Way! has four primary outcome areas: education, employment, healthy routines, and positive help-seeking behavior.

#### Usual services

Usual Services (US) comprise of a variety of services that are currently being provided for youth transitioning from out-of-home care within the Swedish social services or civil society. Interventions provided as part of US can be for example housing solutions in group homes or individual apartments with support from assigned staff members, or mentorship programs. Most Swedish Social services provide interventions with unspecified or undocumented content [40].

### Outcomes

#### Primary outcomes

All primary outcomes concern the youth participants.

**General Self-Efficacy Scale (GSE)** reflects an optimistic self-belief that one can perform a novel or difficult task, or cope with adversity [41]. Perceived self-efficacy eases goal-setting, effort investment, robustness in the face of barriers and recovery from setbacks. The scale consists of 10 items rated on a four-point sematic scale (“not at all true” to “exactly true”). A high score indicates high self-efficacy. The Swedish version was translated by Koskinen et al [42].

**Resilience Scale (RS-14)** reflects the degree of individual resilience, a positive personality characteristic that enhances adaptation [43, 44]. The scale consists of 14 items rated on a seven-point sematic scale (“disagree” to “agree”). A high score indicates high resilience. The Swedish version was translated by Lundman et al [45].

**The Need Satisfaction and Functional Scale (NSFS-18)** measures external motivation from three perspectives in three subscales: autonomy (the need that your own actions are self-initiated and self-regulated), social relatedness (the need in your own social environment to develop secure and satisfying connections), and competence (the need that you preform necessary actions with efficiency, [46]). The scale consists of 18 items rated on a five-point sematic scale (“agree” to “disagree”). A high score indicates high autonomy, social relatedness, or competence. The Swedish version was translated by Aurell et al [47].

#### Secondary outcomes

All secondary outcomes concern the youth participants.

**Daily Life Routines (DLR-18)** was inspired from the Sustainability of Living Inventory [48] but shortened and adjusted to fit youth’s everyday life. The total score of 18 items spans over areas of Personal Hygiene, Eating Habits, Sleeping Habits, Household Chores, Physical Activates, and Social Activities. A high score indicates robust routines. This version was developed by us.

**Social Support Questionnaire (SSQ-6)** maps the number of available others the respondent can turn to and the degree of satisfaction with the perceived support [49]. The number of support persons score assesses the number of available others the respondent feels he or she can turn to in times of need in each of six situations. The satisfaction score measures the respondent’s degree of satisfaction with the perceived support available in that particular situation. A high score indicates several support persons or high satisfaction. The Swedish version was translated by us.

**General Health Questionnaire 12** (GHQ– 12) is a screening instrument to detect psychosomatic symptoms and conditions [50]. The scale consists of 12 items phrased as statements about symptoms with four sematic response options on a four-point scale. Among the items, six are positively phrased and six are negatively phrased, but worded so there is no need to reverse scores. A high score indicates more psychosomatic symptoms. The Swedish version was purchased through https://mapi-trust.org.

**General Help Seeking Questionnaire (GHSQ)** assesses intentions to seek help from different sources including both formal and informal help source options [51]. The GHSQ uses a matrix format that can be modified according to purpose and needs to meet sample characteristics and study requirements. A high score indicates high intentions to seek help. The Swedish version was translated by us.

#### Other outcomes

*Youth self-reported measures*. ***Client Satisfaction Questionnaire (CSQ-8)*** assesses client satisfaction with services received by respondents [52]. The scale consists of eight items rated on a four-point sematic response option scale. A high score indicates high satisfaction. The Swedish version was purchased from https://csqscales.com.

*Youth level register data*. In order to assess longer-term outcomes, we will as part of this study collect specific variables from a number of official registers:

***LISA*** (Swedish acronym, *sv*. Longitudinell Integrationsdatabas för Sjukförsäkring- och Arbetsmarknadsstudier; *eng*. Longitudinal Integration Database for Health Insurance and Labor Market Studies) is a national registry database held by Statistics Sweden (https://www.scb.se/vara-tjanster/bestall-data-och-statistik/bestalla-mikrodata/vilka-mikrodata-finns/longitudinella-register/longitudinell-integrationsdatabas-for-sjukforsakrings—och-arbetsmarknadsstudier-lisa/) The database makes it possible to follow, over time, a person’s transitions between, for example, gainful employment, unemployment, sick leave and illnesses. Variables on education and training, employment and unemployment as well as income and social insurance can be used as outcomes.

***RAKS*** (Swedish acronym, *sv*. Registerbaserad AKtivitetsStatistik, *eng*. Register-based ACtivity Statistics) is a national registry database held by Statistics Sweden (https://www.scb.se/vara-tjanster/bestall-data-och-statistik/bestalla-mikrodata/vilka-mikrodata-finns/individregister/mikrodata-for-registerbaserad-aktivitetsstatistik-raks/). RAKS is a compilation and further development of variables that are already in the e.g., LISA database. The object is to describe an individual´s total livelihood and connection to the labor market. Two outcome variables of interest can be: establishment within the employment market and main source of income.

***Participation in Education*** (*sv*. Registerbaserad AKtivitetsStatistik) is a national registry database held by Statistics Sweden (https://www.scb.se/vara-tjanster/bestall-data-och-statistik/bestalla-mikrodata/vilka-mikrodata-finns/individregister/registret-over-befolkningens-studiedeltagande/). The statistics are based on registers for students in upper secondary school, adult education, qualified vocational education, labor market education and university and college. The information contained in this database enables the ability to describe the type of education, place of study, existence of study grants or loans, and educational provider for each individual within the study.

***Criminality*** is a combination between two ntional registry databases (*sv*. Belastningsregistret and *sv*. Misstankeregistret) held by the Swedish Police (https://polisen.se/lagar-och-regler/behandling-av-personuppgifter/polisens-register/). The registers contain information on whether a person has had criminal convictions, approved penalty orders and administrative fines, but also if they have been reasonably suspected of a crime or have been requested to be surrendered or extradited for a crime (with the exceptions of traffic violations). Only individuals over the age of 15 can be included in these registers.

***Hospital care*** derives from the national Patient registry (*sv*. Patientregistret) held by the National Board of Health and Welfare (https://www.socialstyrelsen.se/statistik-och-data/register/patientregistret/). The register contains both an individual´s outpatient and inpatient care. The registry contains variables such as duration of care, type of care, care disruption, diagnoses, and medication.

Register data will be collected 24 months after T1 for all youth who have consented to participate in the study, regardless of whether they have completed T2 and T3 or not.

*Service provider level implementation measures*. Service providers delivering *My Choice–My Way*! fill out the following implementation outcome measures post T2 based on Weiner et al. [53] on 5-point Likert scales: Acceptability of Intervention Measure (AIM, 4 items), Intervention Appropriateness Measure (IAM, 4 items), and Feasibility of Intervention Measure (FIM, 4 items).

Intervention dose estimation framework and tool assess intervention duration, percentage of intervention delivered, number of sessions (3 items).

#### Systematic session observation

Two sessions per youth will be randomly selected in the My Choice-My Way! arm of the study. The service provider will make a video recording of themselves (i.e., no video recordings of youth participants) providing the session to participant youth. The recordings will be sent to the research team for analysis of fidelity to model based on a structured assessment instrument.

### Participant timeline

The study will be conducted over the course of 24 months. Time schedule of enrolment, interventions, assessments, and visits for participants are presented in Fig 1. The start of the recruitment period for this study is October 2, 2022, and the prospective end of the recruitment period for this study is December 31, 2023.

**Fig 1 pone.0293952.g001:**
[figure not shown]
Schedule of enrollment, interventions, and assessments. 1. During the period between T1-T2. 2. PostT2.

### Sample size

Following Cohen’s proposed interpretation of *f*, this study will need a minimum of 124 youth to fully participate (complete) in the effectiveness trial in order to test within and between interactions over three measurement points [54, 55]. Assuming a 20% drop out rate, we aim to recruit 80 youth per study arm. This will result in 85% statistical power to detect a medium (*f* > .25) effect with alpha set at .05 for a repeated measures ANOVA with within and between interactions.

Service provider sample size is based on the ratio of service provider to youth participant referred to the study.

### Recruitment

Youth are recruited directly by participating youth service organizations. Organizations are self-referred to receive training in My Choice–My Way!. This is following a wide scale recruitment effort conducted via announcements on social media, direct contact to national, regional, and local youth serving and policy organizations. Youth are informed about the study verbally and in writing and subsequently asked if they are interested in participating by staff at the participating organizations (i.e., service providers). Participating organizations are responsible for recruiting service providers that are deemed suitable to work with delivering the intervention.

### Allocation

This study will follow the natural assignment of youth to condition (i.e., the research team will not manipulate the normal operating procedures of the participating municipalities/organizations but instead will follow youth as they are assigned to My Choice–My Way! and US). We will implement a rolling inclusion. Youth will be admitted to the study as they are referred to one of the study arms (My Choice–My Way!, US). Inclusion to the study will continue until we have included the desired number of participants.

### Data collection methods

Youth level data will be collected through a digital questionnaire at three (i.e., T1, T2, T3) time points. First, pre-test measurements (T1), directly following the informed consent procedure but prior to program start. Post-test measurement (T2), after completion of My Choice–My Way! (approximately 8 months after T1, standardized across groups). Third, follow-up measurements (T3), 9 months following T2. Youth level register data will be collected 24 months after T1.

Upon declaration of interest to participate in the study, the youth will be given the option to give their informed consent and fill in the baseline questionnaire electronically via a link received through e-mail or over the phone with a member of the research team. Each youth who chooses to participate will receive compensation for their time upon filling out each questionnaire (approximately $20). Participants are able to choose between receiving compensation in cash or in the form of a gift card.

Service providers of My Choice—My Way! will be asked to complete a questionnaire post-T2 data collection investigating key determinants of implementation success.

### Statistical methods

#### Aim 1 statistical methods

*Baseline characteristics*. Demographic/background and T1 values on outcome variables will be investigated for the entire group and each arm separately.

*Baseline differences in between-group analyses*. Baseline differences on background and outcome variables between groups at T1 (due to the absence of randomization) will be investigated (e.g., *x2*, *t*-test, Mann-Whitney U). Any identified differences will be statistically controlled for in between group analyses.

*Attrition*. Analysis of within group and between group attrition will be conducted (i.e., differences in baseline characteristics of those that remain in study and those that drop out e.g., *x2*, *t*-test, Mann-Whitney U).

*Intent-to-treat (ITT)*. All analyses will be conducted with an ITT approach and missing values on follow-up data will be imputed using the maximum likelihood (ML) approach.

*Sensitivity analysis*. All results will be investigated through sensitivity analysis for their robustness to assumptions and method choices made during the course of the study (e.g., results with imputation vs results without imputation, changes in resource use and cost data).

*RQ1*. The relative effectiveness of My Choice–My Way! and US will be assessed by analyzing within group and between-group changes on participant self-reported and register data after T2 and again after T3 data collection using e.g., ANOVA, ANCOVA depending on final data characteristics.

*RQ2*. Participant characteristics measured at T1 (e.g., gender, age, type of placement) to will be analyzed (e.g., regression-based moderation analysis, ANCOVA depending on final data characteristics) for their moderating effect on changes in self-reported and register data collected at T2 and T3.

*RQ3*. Service provider reported implementation measures (i.e., acceptability, appropriateness, feasibility) and fidelity scores from the systematic session observations will be analyzed (e.g., regression-based moderation analysis, ANCOVA depending on final data characteristics) for their moderating effect on changes in participant self-reported and register data collected at T2 and T3.

*RQ4*. Cost analysis will include the resources necessary to provide the intervention along with a comparison of the relative cost-effectiveness of the intervention compared to the control condition. The incremental costs of providing the intervention will be assessed prospectively considering incremental changes in youth outcomes through economic analysis (e.g., cost-benefit, cost-effectiveness, or cost-consequence depending on final outcome).

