### Study setting

This is a multicenter research project that will be conducted at a total of 21 research sites throughout Sweden. Organizations have naturally self-selected to either implement My Choice–My way! (*n* = 12) or to continue providing Usual Services (US, *n* = 9). All twelve organizations that implement My Choice—My Way! are part of the Swedish social services, although some are public and others private providers of services to youth. The nine organizations that constitute the control group and provide US are various organizations that provide support for the target group either within the Swedish social services or as a part of civil society. A list of study sites can be obtained from the first author of this protocol.

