#### Youth participants

All youth in Sweden aged 15 years or older living in out-of-home care and placed by participating organizations, or who self-refer to the services provided by participating organizations, will be eligible for participation and invited to participate. Additional inclusion criteria for participating in My Choice–My Way!: the youth have the ability to spend periods of time outside of placement (i.e., institutional placement) without incident as determined by referring social worker. My Choice–My Way! should never be provided as a replacement for existing treatment services within the organization. Although our goal is to open inclusion to all youth aged 15 or older in out-of-home care, certain unforeseen characteristics may necessitate development of exclusion criteria (e.g., presence of severe intellectual disability).

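### Letting T1 comparisons decide which variables are controlled, and leaving ANOVA or ANCOVA open until the data are seen, can leave measured confounding in this non-randomised comparison

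*Protocol article*

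**What the plan says.** Arms are not randomised. Under Allocation: "This study will follow the natural assignment of youth to condition". Under Study setting: "Organizations have naturally self-selected to either implement" the programme (12 sites) or to carry on with usual services (9 sites). Under Youth participants, the programme arm alone has a further criterion, judged by the referring social worker: "the youth have the ability to spend periods of time outside of placement".

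The Aim 1 statistical methods compare background and outcome variables between arms at T1. The comparison is described in these words: "due to the absence of randomization) will be investigated (e.g., *x2*, *t*-test, Mann-Whitney U". The rule that follows is: "Any identified differences will be statistically controlled for in between group analyses".

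For RQ1, within-group and between-group changes are to be analysed "using e.g., ANOVA, ANCOVA depending on final data characteristics". RQ2 names gender, age and type of placement as T1 characteristics, but only as possible moderators. A general sensitivity clause covers "robustness to assumptions and method choices made during the course of the study"; its examples are imputation and cost data. Nothing else in the article fixes a covariate set or a single RQ1 model.

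**The concern.** A between-group test at T1 answers the wrong question for choosing covariates. A non-significant result at this sample size does not show balance. Whether a variable confounds also depends on its link to the outcome, which a baseline test does not examine. The variables most likely to slip through are those with moderate imbalance, and several of them together can shift the effect estimate.

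The open choice of model adds to this. Under randomisation, an analysis of change and an analysis adjusted for T1 have the same expected treatment effect. In self-selected groups with unequal T1 outcomes they do not, so a choice made on the final data is also a choice between two effect estimates.

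This rule governs the main comparison of the study, and the article itself links the T1 check to the lack of randomisation.

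**Working it through.** **The plan's own figures.** Sample size states "this study will need a minimum of 124 youth to fully participate (complete) in the effectiveness trial", with 20% dropout and 80 recruited per arm. 124/0.8 = 155, so recruiting 160 is consistent, and 160 × 0.8 = 128 would complete. The figure of 124 cannot be reproduced exactly because no within-person correlation is given: for 85% power, a between-group effect in a three-point repeated-measures ANOVA needs 118 at a correlation of 0.7 and 128 at 0.8. The present point does not depend on it. The planned f = 0.25 equals d = 2 × 0.25 = 0.5 for two groups, which serves as a yardstick below.

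**Step 1: how often a T1 test misses an imbalance.** Assume that identified means two-sided p<0.05. With n per arm and a true imbalance of d SD, t is noncentral with parameter d√(n/2) and 2n − 2 df. For n = 80 and d = 0.3 the parameter is 0.3 × √40 = 1.897, the critical value is 1.975, and P(|t| < 1.975) = 0.529.

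| True imbalance | Missed, 80 per arm | Missed, 62 per arm |
|---|---|---|
| 0.2 SD | 76% | 80% |
| 0.3 SD | 53% | 62% |
| 0.4 SD | 29% | 40% |

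Three independent confounders at 0.3 SD are all retained with probability about 0.471³ = 0.10.

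**Step 2: what this does to the estimate.** The documents give no imbalances or outcome correlations, so these are assumptions: 80 per arm, true effect zero, three confounders each imbalanced by 0.3 SD, joint correlation 0.5 with the T2 outcome, and a confounder kept only if its T1 test gives p<0.05. Simulated results for the analysis of change:

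| Confounders' effect at T1, relative to T2 | Residual bias (SD) | Type I error |
|---|---|---|
| Equal | −0.004 | 5.8% |
| Half | 0.044 | 5.5% |
| None | 0.081 | 8.4% |

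With ANCOVA on T1 and the same selection rule, bias is about 0.02 to 0.08 SD. Across both models, type I error runs from about 5% to 9–10%. Adjusting for all three regardless of the tests gives bias near 0 and type I error of about 5%. The upper bias is 0.08/0.5 = 16% of the planned effect.

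The bias is smaller than the miss rate suggests, because the confounders that are dropped are those whose observed imbalance happened to be small.

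**Step 3: the choice of model.** With a T1 outcome gap D and pre–post correlation ρ (equal SDs), change-score ANOVA and ANCOVA differ by D(1 − ρ). For an assumed D = 0.3:
- ρ = 0.3: 0.3 × 0.7 = 0.21 SD
- ρ = 0.5: 0.3 × 0.5 = 0.15 SD (0.15/0.5 = 30% of the planned effect)
- ρ = 0.7: 0.3 × 0.3 = 0.09 SD

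This applies to gaps that are not identified, since an identified one must be controlled. At p<0.05 the largest observed gap that escapes is 1.975 × √(2/80) = 0.31 SD, so D = 0.3 is close to the worst case.

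**The case against.** Several points against the concern stand.

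- **The threshold is inferred.** The tests are given as examples, and the rule does not say that only significant differences count. No other route to adjustment is described, however, so a test-based reading is the natural one.
- **T1 scores are not ignored.** A reader might infer that the T1 outcome enters only if it differs significantly, that the precision from T1 scores is given up, and that covariate adjustment is the only protection against selection. The documents do not support this. The trial design has pre-, post- and follow-up measures, the sample size is for a repeated-measures ANOVA, and RQ1 analyses changes. T1 scores therefore enter either way, and analysing change removes confounding that acts equally at T1 and later.
- **The size is scenario-dependent.** The 0.08 SD bias lies at the unfavourable end. It arises when T2 levels are analysed without T1, or when the confounders have no effect at T1.
- **The model choice is partly constrained.** The rule covers outcome variables as well as background variables, so an identified T1 gap points to ANCOVA.
- **A condensed article may leave the final model to an analysis plan.** That excuses an omission, but this is a stated rule, and an analysis plan that followed it would inherit the weakness. The sensitivity clause does not mention the covariate set.

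**Conclusion.** The point holds as a risk: the stated rule can leave measured confounding in the effect estimate. The article does not show that it will. Under the assumed scenarios the residual bias is about 0 to 0.08 SD, and type I error rises from about 5% to at most 9–10%. These figures rest on a p<0.05 threshold, three confounders at 0.3 SD and a joint correlation of 0.5, none of which the documents state. Separately, an unidentified T1 outcome gap makes the two candidate models differ by up to about 0.15 SD at ρ = 0.5.

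A reader might also infer that naming covariates in advance would make the comparison unbiased. It would not: the near-zero bias in the check holds only because every simulated confounder was measured. Self-selection of organisations and the arm-specific eligibility judgement remain. The rule should be fixed, but it does not by itself invalidate the plan.

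**What to change.** Replace the test-then-adjust rule with the following:

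1. Name one primary model for the arm difference at T2 and T3.
2. Always include the T1 value of the outcome and a short set of prognostic T1 variables named in advance from those already collected (for example age, gender and placement type), whatever the T1 tests show.
3. Describe baseline balance with standardised differences instead of p-values.
4. Keep the change-score analysis as a named sensitivity analysis.
5. State in the report that unmeasured and organisation-level selection remains, including the self-selection of sites and the extra criterion in the programme arm.

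The cost is analysis wording and a few model degrees of freedom. No new data are needed, since RQ2 already lists these characteristics as measured at T1.

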### Trial design

The study can be described as a hybrid effectiveness-implementation study with natural controls in a quasi-experimental two-arm study design [30]. We will conduct such a study to test the impact of the leaving care interventions while we at the same time collect data on the implementation process and outcomes (i.e., Hybrid I design). Research design and methods for data analysis specifically linked to each of the aims and research questions will be described in more detail below.

#### Design Aim 1

We will perform an effectiveness study to achieve Aim 1 and to answer RQ1-RQ4. The effectiveness study will be carried out as a natural quasi-experiment with two groups of youth participants (My Choice–My Way!, US) with dependent pre-, post- and follow-up measures [31] (i.e., 3 x 3 mixed factorial design. Long-term outcomes will be studied with a longitudinal register study.

#### Design Aim 2

Based on the My Choice–My Way! theory of change (i.e., logic model, [32]) salient change mechanisms will be chosen and measured.

#### Design Aim 3

Posttest comparison study comparing implementation and youth level outcomes for organizations engaged in implementation support with organizations not receiving implementation support.

#### Design Aim 4

Qualitative implementation, posttest interview study with service providers.

#### Design Aim 5

Qualitative implementation, posttest interview study with youth participants.

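### In a self-selected comparison the article adjusts only for differences identified at T1, gives the registers an outcome role only, and names no analysis aimed at unmeasured confounding

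*Protocol article*

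**What the plan says.** The Trial design section describes "natural controls in a quasi-experimental two-arm study design", and its Aim 1 part sets two groups of youth "with dependent pre-, post- and follow-up measures". Under Study setting, "Organizations have naturally self-selected to either implement" the programme (12 organisations) or to continue with Usual Services (9). Under Allocation, "This study will follow the natural assignment of youth to condition".

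Eligibility differs by arm. The Youth participants section adds a condition for My Choice–My Way! only: that "the youth have the ability to spend periods of time outside of placement" without incident, as judged by the referring social worker.

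Aim 1 statistical methods states how confounding is handled. Background and outcome variables are compared between arms at T1, explicitly because there is no randomisation, and identified differences are controlled for in the between-group analyses. The sensitivity paragraph then says: "All results will be investigated through sensitivity analysis for their robustness to assumptions and method choices made during the course of the study". Two illustrations follow: results with and without imputation, and changes in resource use and cost data.

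The registers are introduced under Other outcomes: "In order to assess longer-term outcomes, we will as part of this study collect specific variables from a number of official registers". On timing, "Register data will be collected 24 months after T1 for all youth who have consented to participate in the study", whether or not they completed T2 and T3. RQ1 to RQ3 use register data only on the outcome side. No look-back window is stated, and no register variable is named as a covariate.

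**The concern.** The main comparison rests on the assumption that, given what is measured and adjusted for at T1, the arms do not differ in anything that predicts later self-efficacy, resilience or need satisfaction. There are concrete reasons to doubt it. Organisations that sought training may serve different youth from those that did not. The comparison arm includes civil-society providers. The arm-specific condition lets a social worker's judgement of behaviour outside placement decide who can enter one arm.

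T1 scores on the three primary scales need not carry all of that history. By the article's own description, the registers hold related information: outpatient and inpatient care, diagnoses, education, suspected offences and convictions. The study already plans to obtain these registers but gives them no part in adjustment. If history differs between arms and predicts change beyond the T1 score, a difference on GSE, RS-14 or NSFS-18 would partly reflect who was enrolled.

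**Working it through.** The plan gives no figure for confounding, so there is none to reproduce. The calculation below is illustrative and shows only how sensitive the test would be.

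**Inputs from the article (Sample size).** 80 youth recruited per arm; 20% dropout, so 80 × 0.8 = 64 completers per arm (128 in total, above the stated minimum of 124); alpha 0.05; target effect f = 0.25, which for two equal groups is d = 2f = 0.5 SD.

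**Assumptions, not in the documents.**
- Correlation of 0.5 between T1 and the later score.
- A binary history factor 15 to 20 percentage points more common in one arm.
- That factor is worth 0.2 to 0.5 SD on the outcome after T1 adjustment.
- Youth are treated as independent, ignoring clustering within the 21 sites.

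**Bias = prevalence difference × effect given T1.**
- Weak factor (0.2 SD): 0.15 × 0.2 = 0.03 SD; 0.20 × 0.2 = 0.04 SD.
- Strong factor (0.5 SD): 0.15 × 0.5 = 0.075 SD; 0.20 × 0.5 = 0.10 SD.
- Two strong factors, additive and in the same direction: 0.15 and 0.20 SD.

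**Standard error = sqrt(1 − 0.5²) × sqrt(2/n).**
- n = 80: 0.866 × 0.158 = 0.137 SD.
- n = 64: 0.866 × 0.177 = 0.153 SD.

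**Rejection rate when the true effect is zero = P(|Z + bias/SE| > 1.96).**

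| Bias (SD) | 80 per arm | 64 per arm |
|---|---|---|
| 0.03 | 5.6% | 5.4% |
| 0.04 | 6.0% | 5.8% |
| 0.075 | 8.5% | 7.8% |
| 0.10 | 11.3% | 10.0% |
| 0.15 | 19.5% | 16.5% |
| 0.20 | 30.9% | 25.7% |

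A bias of 0.20 SD is 0.20/0.5 = 40% of the effect the trial is sized to detect.

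**How well the T1 comparison finds imbalance.** With 80 per arm, a 5% two-sample test has about 24%, 48% and 89% power for a T1 imbalance of 0.2, 0.3 and 0.5 SD. Moderate imbalance, even in measured variables, can go unidentified and so unadjusted.

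**How well a falsification check would work.** Suppose a pre-T1 register outcome, which the programme cannot have affected, is compared between arms. With 80 per arm and a base rate of 20% to 40% (assumed), power is about 57% down to 48% for a 15-point difference and about 79% down to 72% for 20 points.

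**The case against.** A reader might infer that the plan never tests its key assumption and contains nothing that would reveal selection. The documents do not support that, for three reasons.

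- The sensitivity promise covers all results and robustness to assumptions. Imputation and costs are offered as examples, and a full protocol or analysis plan, not shown, may name more. What can be said is that the article names no such analysis.
- All three primary scales have a T1 value, and the arms are compared on those values and on background variables, with adjustment for differences found. Part of any selection would therefore be seen and handled. Only confounding that remains after T1 adjustment is at issue.
- The absence of unmeasured confounding cannot be tested directly by any method. Register history can turn some unmeasured factors into measured ones or provide a falsification check, but no more.

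Other parts of the objection also stand. The upper figures need a factor worth 0.5 SD after T1 adjustment, as large as the trial's whole target effect, and the two largest need two such factors acting together. At 0.2 SD the inflation is slight. Register history is limited for the youngest: the crime registers start at age 15, and the education register is described as covering upper secondary school onward. The look-back available and the consent scope are not stated. A falsification check with about even odds of finding a 15-point difference gives weak reassurance when null. When positive, it shows imbalance in that variable, not bias in a T1-adjusted scale.

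The objection does not remove the core point. The confounding strategy and the purpose of the registers are stated choices in the article, and together they leave relevant pre-T1 history out of the main comparison.

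**Conclusion.** The point holds in limited form. The article fixes a self-selected comparison with an arm-specific entry condition, limits its stated confounding control to differences identified at T1, assigns the registers to outcomes only, and names no analysis aimed at unmeasured confounding. Adding pre-T1 register history would improve the stated method.

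The documents do not show that the result will be biased, or by how much. Under the assumed 0.03 to 0.20 SD, the false-positive rate would be about 5% to 26% at 64 completers per arm and 6% to 31% at 80. The lower end is close to nominal. The benefit of adjustment depends on how much of any bias the register variables capture, which is also unknown.

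The matter is best settled before the register order is placed, because the look-back window and its consent cover may be hard to change at the analysis stage.

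**What to change.** 1. State a pre-T1 window for the register extraction already planned at 24 months, as far as consent and ethics scope allow. RQ1 already speaks of changes in register data, which implies an earlier value.
2. Include a short, prespecified set of pre-T1 register variables in the RQ1 between-group models alongside the T1 values: outpatient and inpatient care and diagnoses, with education and offences only where the youth was old enough to be registered.
3. Name one quantitative bias analysis for the primary outcomes, reporting how strong a residual confounder would have to be to remove each result.
4. Optionally, hold one pre-T1 register outcome out of the adjustment set and report the arm difference as a supportive falsification check. State that power is only about 50% for a 15-point difference with 80 per arm, so a null result is weak reassurance.

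The cost is a longer look-back in the register order, a possible ethics or consent amendment, and a few extra terms in models with about 128 completers, which is why the covariate set should be short and fixed in advance.
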